### Economic evaluation

To confirm the cost-effectiveness of the intervention in this clinical trial versus existing treatment (usual care), an economic evaluation will be conducted concurrently with the clinical trial. The primary economic endpoint of the study is cost per Quality Adjusted Life Years (QALY) gained. To calculate QALY, quality of life will be derived from the EuroQol five dimensions questionnaire (EQ-5D) using area under the curve method [26]. The secondary economic endpoint of the study is cost per the EuroQol Visual Analogue Scale (EQ-VAS). The cost will be determined as follows: (1) the treatment cost incurred in relation to the clinical trial will be calculated by combining the number of treatments and the unit cost, and (2) the treatment cost incurred within the clinical trial institution will be recorded by the researcher by examining the EMR after unblinding.

FAS analysis will be used for economic evaluation, while PP analysis will be used to test the sensitivity of the analysis results to missing values. The primary evaluation period will be 12 weeks, which corresponds to the study’s total follow-up period. If an evaluation needs to be done after 12 weeks, the costs and effects will be extrapolated and estimated using a regression model, or a secondary analysis, such as decision modeling analysis. If the total analysis period (time horizon) exceeds 12 months, the cost unit will be unified into Korean currency (won) in 2021, and a 5% discount rate will be applied based on the Health Insurance Review and Assessment Service economic evaluation guidelines.

The findings of the economic analysis will be presented as follows: (1) a table displaying analysis results, including the incremental cost-effectiveness ratio, (2) a cost-effectiveness plane containing confidence intervals confirmed by non-parametric methods, (3) the Cost Effectiveness Acceptability Curve (CEAC), which measures cost-effectiveness sensitivity to changes in national thresholds, and (4) a graph displaying the value of information analysis results, which can be used to estimate the value of information for the target population group.

The level of statistical significance will be tested using a p-value of .05 or less. For the analysis, Stata-MP version 14 (StataCorp LLC, College Station, Texas, USA) and R version 4.0.2 (R Foundation for Statistical Computing, Vienna, Austria) will be used. TREEAge Pro 2016 (TreeAge Software Inc., Williamstown, MA, USA) will be used for extrapolation through modeling, when necessary.

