### Participant timeline

Among patients who applied to participate in this trial and signed the ICF, the following items will be checked for eligibility assessment: vital signs, the HY scale, the MMSE-K, demographic survey, medical and treatment history, laboratory tests, electrocardiogram, and chest X-ray. Upon random assignment to either the experimental or control group, participants will undergo treatment for a duration of 8 weeks in accordance with their respective group assignments. The MDS-UPDRS Part III, IPAQ, PSQ, PDSS, and economic evaluation questionnaire will be administered four times (0th, 4^th^, 8^th^, and 12^th^ week). TUG, GAITRite, and fNIRS measurements will be taken three times (0^th^, 8^th^, and 12th week). Gut microbiome specimens will be collected and analyzed twice: once at baseline and once at 8^th^ week. Before collecting human specimens, additional consent will be obtained for collection and use of biological specimens.

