### Sample size

The hypothesis of this clinical trial is as follows:

H0 (null hypothesis): μ_t_ = μ_c_H1 (alternative hypothesis): μ_t_ ≠ μ_c_

μ_t_ denotes the average change in MDS-UDPRS Part III score from baseline to 8 weeks in the treatment group (MARS-PD treatment), and μ_c_ denotes the average change in MDS-UDPRS Part III score from baseline to 8 weeks in the control group (usual care). The experimental and control groups will be recruited in a one-to-one ratio.

For the determination of the sample size, we referenced a previous study that closely resembled our current investigation in terms of research design, treatment period, treatment method, number of participant visits, and outcome variables [21]. In the study conducted by Hackney and Earhart, a total of 33 patients diagnosed with PD were enrolled, with 17 participants in the exercise (Tai Chi) group and 16 in the control (no intervention) group. The treatment period lasted 10–13 weeks, with a total of 20 treatment sessions. One of their outcome variables was the UPDRS motor subscale (Part III). The observed average change in UPDRS Part III scores for the treatment and control groups were -1.5 ± 6.6 and 4.3 ± 5.6, respectively. The mean difference in effect between the Tai Chi group and control group was calculated as 5.8, with a pooled standard deviation was 6.1. These parameters from the previous study served as a basis for informing the sample size calculation in our current research design.

We used a conservative value of 5 for the mean difference of the effect and 6.5 for the standard deviation to calculate the number of test subjects to confirm the effect of the experimental group compared to the control group in this study. According to Shulman et al. [22] and Sánchez-Ferro et al., [23] the minimal clinically important difference (MCID) for UPDRS Part III is 2.3 and 5, respectively. In the meantime, Horváth et al. [24] estimated that the MCID for MDS-UPDRS Part III is between 2.3 and 2.7 points. Therefore, the proposed mean difference of the effect of 5 is equal to or greater than the MCID that was previously reported by the studies. Substituting this into the calculation formula [25] results in approximately 36 people per group as shown below. Considering the dropout rate of 20%, a total of 88 clinical trial subjects, 44 per group, are required. The criteria for dropout is specified in the protocol (S2 Appendix).

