### Efficacy evaluation

The primary outcome, the mean change in MDS-UPDRS Part III score from baseline at 8 weeks between the experimental and control groups will be assessed using an independent t-test. If there is a significant difference in the baseline between the groups, we will use an analysis of covariance. If there is a significant difference in the other baseline variables, we will employ multiple regression analysis. The MDS-UPDRS Part III scores will be assessed at each time point within the confines of a linear mixed effects model with fixed effects for treatment, time, and the interaction of treatment by time, and an unstructured covariance structure for repeated measures within each subject.

The secondary outcomes include the MDS-UPDRS, IPAQ Short Form, PSQ, PDSS, TUG results, GAITRite parameters, fNIRS measurements, number of steps per day, gut microbiome analysis results, and iris connective tissue texture and density. To evaluate the secondary outcomes, we will use analysis of covariance or multiple regression analysis with corrected baseline variables. When the baseline variable is used as a covariate, a PP analysis will be performed without processing missing values.

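### The article states no adjustment for baseline EQ-5D in the QALY comparison; prespecifying one would make the primary economic endpoint more precise at no cost in data

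*Protocol article*

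**What the plan says.** In the Protocol article, Economic evaluation: "The primary economic endpoint of the study is cost per Quality Adjusted Life Years (QALY) gained". The construction of the QALY is given as "quality of life will be derived from the EuroQol five dimensions questionnaire (EQ-5D) using area under the curve method", with a literature citation. On the horizon: "The primary evaluation period will be 12 weeks, which corresponds to the study’s total follow-up period". On the analysis sets: "FAS analysis will be used for economic evaluation, while PP analysis will be used to test the sensitivity of the analysis results to missing values". Listed next are the outputs: a results table with the incremental cost-effectiveness ratio (ICER), a cost-effectiveness plane with non-parametric confidence intervals, an acceptability curve (CEAC) and a value-of-information graph. No baseline term appears, and nothing rules one out.

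Under Participant timeline, the "economic evaluation questionnaire will be administered four times", at weeks 0, 4, 8 and 12. A baseline EQ-5D value should therefore be available; the area-under-the-curve method needs one in any case.

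Under Efficacy evaluation, for the clinical secondary outcomes, "we will use analysis of covariance or multiple regression analysis with corrected baseline variables". EQ-5D and QALYs are not in the list of outcomes to which that sentence applies.

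**The concern.** Week 0 is itself a point on the utility curve, and patients who start with higher utility tend to stay higher. If QALYs are compared between arms without a baseline term, a chance difference in baseline EQ-5D enters the incremental QALY twice: directly through the week-0 weight, and indirectly through the correlated later values. The incremental QALY is the denominator of the ICER and one axis of the cost-effectiveness plane. Over 12 weeks it can only be small, so a modest baseline difference may matter relative to it.

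Followed literally, the economic section leads to that raw comparison, while the article plans baseline correction for its clinical secondary outcomes. What is at stake is the precision of the primary economic result, and how to read it if the arms happen to differ at baseline.

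**Working it through.** **Inputs from the article.** Visits at weeks 0, 4, 8 and 12; horizon 12 weeks; 44 per arm ("Considering the dropout rate of 20%, a total of 88 clinical trial subjects, 44 per group, are required").

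The sample size reproduces: 2 × (1.96 + 1.28)² × 6.5² / 5² = 35.5, so 36 per arm; 36 × 1.2 = 43.2, so 44. It rests on MDS-UPDRS Part III alone ("We used a conservative value of 5 for the mean difference of the effect and 6.5 for the standard deviation"). The article gives no SD, target effect or sample size for EQ-5D or QALYs.

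**Assumed inputs, none from the documents.** Utility SD 0.15; equal correlation r between any two visits, 0.6 to 0.8; utility gain d of 0.03, 0.05 or 0.10, with half reached at week 4 and all of it at weeks 8 and 12.

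**Weights.** The trapezoid rule gives 2, 4, 4 and 2 weeks, each divided by 52, for weeks 0, 4, 8 and 12. They sum to 12/52 = 0.231 years.

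**Baseline imbalance.** SE of the baseline difference = 0.15 × √(2/44) = 0.032.

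**Carry into the QALY difference** = (2 + 10r)/52 × imbalance. For one SE:
- r = 0.6: 8/52 × 0.032 = 0.0049
- r = 0.8: 10/52 × 0.032 = 0.0062

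**QALY value of a real gain** = (4 × d/2 + 4d + 2d)/52 = 8d/52:
- d = 0.03: 0.0046
- d = 0.05: 0.0077
- d = 0.10: 0.0154

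**Variance with and without adjustment.** In units of SD² × (2/n)/52², the unadjusted variance is 40 + 104r (40 is the sum of squared weights, 104 the cross terms). Adjustment removes (2 + 10r)².

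| r | Unadjusted | Removed | Left | Ratio | SE unadjusted | SE adjusted |
|---|---|---|---|---|---|---|
| 0.5 | 92.0 | 49 | 43.0 | 0.467 | 0.0059 | 0.0040 |
| 0.6 | 102.4 | 64 | 38.4 | 0.375 | 0.0062 | 0.0038 |
| 0.7 | 112.8 | 81 | 31.8 | 0.282 | 0.0065 | 0.0035 |
| 0.8 | 123.2 | 100 | 23.2 | 0.188 | 0.0068 | 0.0030 |

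The SE columns use SD 0.15 and 44 per arm. The ratio does not depend on the SD or on n.

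**Chance of a wrong-sign QALY difference**, Φ(−effect/SE), for r = 0.6 to 0.8:
- d = 0.03: about 23 to 25% unadjusted, 6 to 11% adjusted
- d = 0.05: about 11 to 13% unadjusted, 0.5 to 2% adjusted

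**Wider range.** Take SD 0.10 to 0.25, r = 0.5 to 0.7 and 44 per arm. The chance that the imbalance error is at least as large as the effect, in either direction, is 11 to 62% for d = 0.03, 1 to 40% for d = 0.05 and 0 to 10% for d = 0.10. With 36 per arm it is 15 to 65%, 2 to 45% and 0 to 13%.

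**The case against.** The strongest reply is that the article is silent, and silence is not a decision against adjustment. The quoted sentence says how each patient's QALY is built, not how the arms are compared, and an area-under-the-curve QALY can be analysed with a baseline covariate. The full protocol (S2 Appendix), any analysis plan and the source cited for the method are not shown, and any of them may specify the model. This stands: a reader might infer that the trial has chosen an unadjusted analysis, and the article does not say so. The sentence on baseline correction in Efficacy evaluation does not contradict the economic section either, because it covers other outcomes.

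A reader might also infer that the unadjusted result would be biased or invalid. It would not be. Randomisation keeps it unbiased on average, and the noise from baseline differences is already part of its standard error, so it would show in the planned confidence intervals and CEAC. The cost is lost precision, together with conditional bias once a particular imbalance has been observed.

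Finally, a reader might conclude that chance imbalance can match the effect the trial is looking for. The only effect sought in the article is 5 points on MDS-UPDRS Part III; no EQ-5D or QALY target exists to compare against.

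What survives is that the section goes into enough detail to name the QALY method, analysis sets, horizon and outputs, yet the step that most affects the precision of the QALY difference is not among them, while the article does give it for the clinical secondary outcomes.

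**Conclusion.** The point holds as a worthwhile improvement, not as an error that invalidates the analysis. As written, the plan leads to a raw comparison of area-under-the-curve QALYs unless a document not shown says otherwise.

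The gain in precision is the firmer result. It depends only on the visit schedule and the assumed equal correlation between visits: about 60 to 80% less variance at correlations of 0.6 to 0.8, and about 50 to 70% less at 0.5 to 0.7.

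The comparison of imbalance with effect is softer, because it also needs an assumed SD and an assumed utility gain. At SD 0.15, a one-standard-error imbalance is similar in size to a gain of 0.03 to 0.05. It slightly exceeds the value of a 0.03 gain and falls short of that of a 0.05 gain, so at one standard error it would not by itself reverse the latter. Against a gain of 0.10 it is minor.

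**What to change.** State in the economic analysis plan, before unblinding, that the incremental QALY will be estimated by regressing each patient's area-under-the-curve QALY on arm and baseline EQ-5D utility. If the non-parametric intervals and the CEAC are produced by bootstrap, refit this regression in every resample so that the plane and the curve use the same adjusted estimate. If the full protocol or an analysis plan already says this, a sentence in the article is enough.

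The cost is one covariate that the visit schedule already provides; no extra data or patients are needed. Fixing it in advance matters, because adding the covariate only after an imbalance has been seen would be a data-driven choice.

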### Interventions

At a 1:1 ratio, patients will be assigned to either the experimental (MARS-PD intervention) or control (usual care with no additional intervention) groups. Those in the experimental group will undergo the MARS-PD intervention twice a week for 8 a span of weeks, totaling 16 visits. The intervention will be administered by Doctors of Korean Medicine with a minimum of one year of clinical experience in the relevant field, as detailed in the authors’ previous work [16]. In contrast, patients in the control group will adhere to their usual care without any supplementary interventions. Given that the number of steps per day constitutes one of our secondary outcomes, all willing participants, regardless of their group assignment, will receive Samsung Galaxy Fit2 smart band (Samsung Electronics Co., Ltd., Suwon, South Korea), and application-based lifestyle guidance.

During the test period, participants are allowed to engage in personal exercise. However, doctor-prescribed manual therapy, exercise therapy, and rehabilitation treatment specifically tailored for PD are not permitted. This restriction aims to maintain consistency in the intervention conditions and isolate the effects of the MARS-PD being evaluated in the trial.

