### Statistical analysis

To calculate compliance for each subject, we will use the following formula:

$$Compliance\left(\%\right)=\frac{number\;of\;interventions\;actually\;conducted}{number\;of\;interventions\;originally\;planned}$$

Throughout the trial, it is imperative that compliance (%) remains at or above 75%. Subjects falling below this threshold will be considered insufficiently compliant and subsequently excluded from the per-protocol (PP) analysis. The efficacy analysis will be primarily assessed based on the full analysis set (FAS) principle, followed by the PP principle for primary and secondary outcomes.

The FAS analysis will be carried out on cases that meet the principle of intention-to-treat (ITT). The FAS analysis will exclude cases falling into the following categories: (1) subjects not meeting the main eligibility criteria, (2) those not receiving the intervention specified in the protocol, and (3) individuals who were never evaluated after randomization with no collectable data.

On the other hand, the PP analysis will be carried out on cases that have successfully completed the entire trial process without any protocol violations. The PP analysis will exclude cases meeting any of the following criteria: (1) subjects dropping out during the intervention period, (2) violation of eligibility criteria, (3) compliance falling below 75%, and (4) any other serious violations of the clinical trial protocol.

By adopting this approach, we aim to evaluate the results conservatively, considering PD’s natural tendency to worsen over time. Statistical analysis will be conducted using the two-tailed test method, and a p-value of < .05 will be deemed statistically significant. In the event of missing values, appropriate imputation methods will be employed based on the underlying cause.

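### The per-protocol analysis named as the economic missing-data check changes the population by adherence and cost, so it cannot isolate the effect of missing values

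*Protocol article*

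**What the plan says.** Under Economic evaluation, the article states that "FAS analysis will be used for economic evaluation" and that the "PP analysis will be used to test the sensitivity of the analysis results to missing values". The primary economic endpoint is cost per QALY, with QALYs derived from EQ-5D. One cost component, the treatment cost of the trial itself, is "calculated by combining the number of treatments and the unit cost"; the other is the cost incurred at the institution, taken from the electronic medical record.

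Under Statistical analysis, the PP set consists of "cases that have successfully completed the entire trial process without any protocol violations", and its listed exclusions are "1) subjects dropping out during the intervention period, (2) violation of eligibility criteria, (3) compliance falling below 75%, and (4) any other serious violations". The FAS already leaves out patients who fail the main eligibility criteria, and also "2) those not receiving the intervention specified in the protocol, and (3) individuals who were never evaluated after randomization with no collectable data". The same section promises imputation suited to the cause of missingness, without naming a method.

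Under Interventions, MARS-PD is given twice weekly for 8 weeks, "totaling 16 visits"; the control arm has no study sessions. Under Participant timeline, the economic questionnaire is due at weeks 0, 4, 8 and 12.

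**The concern.** A sensitivity analysis for missing values should hold the patients fixed and vary what is assumed about the values not seen. Moving from FAS to PP instead changes which patients are analysed, on grounds that are mostly unrelated to missingness. A MARS-PD patient who had 10 sessions and completed every questionnaire has nothing missing, yet is removed.

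The compliance rule also acts on the session count, from which trial treatment cost is calculated. The supposed missing-data check therefore selects on part of the cost outcome, in one arm only.

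What is at stake is the robustness statement that will accompany the cost-effectiveness ratio and acceptability curve. Similar FAS and PP results would be read as evidence that dropout does not matter, and different results as evidence that it does. The contrast supports neither reading. Cost-effectiveness is a stated aim of the trial and the sample size allows for 20% dropout, so the question will arise.

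**Working it through.** **1. What separates PP from FAS**

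| Reason for leaving PP | Defined by missing EQ-5D or cost? | Arm affected |
|---|---|---|
| Dropout during the intervention period | Partly: later questionnaires are likely to be missing | Both |
| Eligibility violation | No | Both |
| Compliance below 75% | No | MARS-PD only |
| Other serious violation | No | Both |

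Only the first row bears on missing data. Nor is PP clearly a complete-case set. A patient lost between weeks 8 and 12 lacks the last economic questionnaire but meets none of the numbered dropout criteria, although the lead sentence of the definition asks for completion of the whole trial.

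**2. The compliance rule in sessions**

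Compliance is sessions conducted divided by sessions planned. With 16 planned, the threshold is 0.75 × 16 = 12, so MARS-PD patients with 11 or fewer sessions are removed. In the control arm the planned number is 0, the ratio is undefined, and the rule has nothing to act on.

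**3. Effect on the intervention-cost component**

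The document gives no figure for this, so there is none to reproduce. Let q be the share of the MARS-PD arm that stops early but remains in FAS, m their mean sessions, and c the mean sessions of those retained. The unit cost is not given, but it cancels from the ratio:

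- FAS mean sessions = (1 − q) × c + q × m
- PP mean sessions = c
- PP/FAS cost ratio = c / [(1 − q) × c + q × m]

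The ratio exceeds 1 whenever m < c. This always holds for patients removed by the compliance rule, because they have at most 11 sessions and those retained have at least 12.

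Assumed inputs (none is in the document): c = 15; m = 4 or 8; q = 0.10 or 0.20.

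| q | m | FAS mean sessions | PP mean sessions | PP cost relative to FAS |
|---|---|---|---|---|
| 0.10 | 8 | 0.9 × 15 + 0.1 × 8 = 14.3 | 15 | 15/14.3 = 1.05 (+5%) |
| 0.10 | 4 | 0.9 × 15 + 0.1 × 4 = 13.9 | 15 | 15/13.9 = 1.08 (+8%) |
| 0.20 | 8 | 0.8 × 15 + 0.2 × 8 = 13.6 | 15 | 15/13.6 = 1.10 (+10%) |
| 0.20 | 4 | 0.8 × 15 + 0.2 × 4 = 12.8 | 15 | 15/12.8 = 1.17 (+17%) |

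With wider assumptions (c = 16, m from 11 down to 1), the FAS mean is 15.5 to 14.5 sessions at q = 0.10, so PP is 3–10% higher. At q = 0.20 the FAS mean is 15.0 to 13.0, so PP is 7–23% higher.

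These shifts occur even if no cost value is missing. They reflect who was removed, not how missing values were treated.

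**The case against.** The strongest defence is that PP is not wholly unrelated to missing data. It drops intervention-period dropouts in both arms. The article promises imputation in general, and under Efficacy evaluation it pairs a PP analysis with leaving missing values unprocessed when baseline is a covariate. If the economic analysis follows that pattern, FAS with imputation against PP without it is a rough comparison of imputed with near-complete data. This stands: PP is a weak, confounded check rather than an empty one. It still says little about data missing not at random, and it cannot separate missingness from adherence and eligibility.

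Four stronger readings may tempt a reader, and the document does not support them:

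- *The main economic result is biased.* It is not affected by this sentence, because FAS is the stated analysis set and PP only the supporting run.
- *Any FAS–PP difference must come from the low attenders.* Dropouts in either arm, including controls, and other violations can contribute as well.
- *Dropouts necessarily lack cost data.* Session counts and the institution's medical record do not depend on attending a study assessment, so EQ-5D is the more likely gap.
- *The percentages carry over to the ratio.* They cover one cost component. Institutional costs, unit cost and QALYs are not quantified.

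The 20% in Sample size is overall dropout, and the document does not say how much of it is partial attendance. Patients who received no intervention are already outside FAS, so not all of the 20% need enter the contrast.

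A separate analysis plan may set out imputation in detail. That would not answer this point, which concerns a method the article states, not a detail it omits.

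**Conclusion.** The point holds as a fault in one stated sensitivity analysis. The FAS–PP contrast mixes missingness with adherence, eligibility and other violations, and its compliance rule selects on a cost component in the MARS-PD arm alone. It cannot support a statement about robustness to missing EQ-5D or cost data, whichever way it comes out.

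The 5–8% and 10–17% figures illustrate the shift in mean intervention cost per MARS-PD patient. They rest on the assumed attendance (15 sessions in those retained, 4 to 8 in stoppers) and stopping shares (10% and 20%). They also read the FAS exclusion for not receiving the intervention as applying to patients with no sessions; a stricter reading would narrow the gap. Neither the size nor the direction of the effect on total incremental cost or on the cost-effectiveness ratio can be derived. The primary efficacy analysis is not involved.

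**What to change.** Replace the sentence under Economic evaluation with three statements:

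1. FAS remains the economic analysis set.
2. Sensitivity to missing values is tested in that same set. Missing EQ-5D values, and any missing costs, are multiply imputed by arm. The imputed values in dropouts are then shifted over a stated range of less favourable values, and the incremental cost, QALY difference and cost-effectiveness ratio are reported across that range.
3. The PP analysis, if kept, is labelled as cost-effectiveness among adherent patients and not as a missing-data analysis.

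The cost is a wording change and a little more programming in the Stata and R software already named; no new data are needed. The downside is that the reported range of cost-effectiveness ratios may be wider or less favourable.
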